### 2.6. Ethical Considerations

The study protocol was approved by the Ethics Committee of the University of Electro-Communications (approval on 16 December 2021; 21068). All the participants provided informed consent. A statement attached to the questionnaire explained the study’s purpose and the voluntary nature of participation and confirmed that the analysis was anonymous. In addition to consent to participate, returning the questionnaire was viewed as consent to participate. All research data are stored on a dedicated computer disconnected from the Internet, and access is exclusively restricted to the members of the research team.

The trial is registered in the UMIN Clinical Trials Registry (UMIN000051393).

### 2.7. Statistical Analyses

All data in the baseline survey are presented as means (standard deviations) or proportions, considering sex differences. The main measures were compared between sexes using the chi-square test for nominal variables and Welch’s *t*-test for continuous variables. A significance level of α = 0.05 indicated statistical significance, and all statistical analyses were performed using IBM SPSS Statistics for Windows, version 29.0 (IBM Corp., Armonk, NY, USA).

As a primary analysis, repeated measures analysis of variance (ANOVA) will be used to verify the interaction between time (pre- and post-intervention) and group (intervention and control groups) to clarify the effect of the interventions on the subjective well-being of older adults after the follow-up survey. In cases where the interaction is significant, a multiple comparison test will be performed using the Bonferroni method. Before ANOVA is performed, propensity score matching with a ratio of 1:1 will be applied using logistic regression based on the baseline survey to reduce bias in background factors between the intervention (participants) and control (non-participants) groups.

A secondary subgroup analysis will be performed to detect differences in the effects of the types of interventions or the intervention frequency on subjective well-being.

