## 2. Materials and Method

### 2.1. Study Design, Study Setting, and Participants

The Chofu-Digital-Choju (CDC; Choju means longevity in Japanese) movement is a quasi-experimental study [18] spanning from January 2022 to March 2024, conducted in collaboration with industry, academia, and the government. The CDC movement aims to foster in-person and online social connections to enhance the subjective well-being of older adults. In January 2022, a survey was conducted by mailing a self-administered questionnaire to collect baseline data for the intervention study. A subsequent follow-up survey, following up on the baseline measurements, is scheduled for a 2-year period.

The study population comprises community-dwelling individuals aged 65–84 years as of 1 October 2022, living independently in two districts of Chofu City, Tokyo, Japan. Individuals older than 85 years were excluded since the response rate that can be employed was extremely low, according to a previous study [19]. These districts were selected through consultation with city and social welfare council employees based on previous surveys and demographic trends. Chofu City, located in the middle of Tokyo (Figure 1), had a population of 238,311 (115,964 men and 122,347 women) as of 1 October 2021, with 51,536 individuals (22,018 men and 29,518 women) aged ≥65 years, constituting 21.6% of older adults [20]. These districts are located in the south and north of the city, where more than half the households reside in apartment buildings and detached houses, respectively [21].

The sample size was determined through several steps, as follows: first, a previous review by Bolier et al. indicated that positive psychology interventions showed an effect size of 0.34 for subjective well-being [22]. To detect this effect using a *t*-test, 137 individuals were required in both the intervention and control groups (with a statistical power of 0.8 and a risk level of 0.05). Second, based on a previous survey [23], we estimated a dropout rate of approximately 20% over 2 years. Third, the expected valid response rate at baseline and follow-up was approximately 80%, based on previous baseline surveys [19,24]. The percentage of participants required in the intervention group was approximately 10% of the total participants. From these estimates, we calculated a baseline survey sample size of 2675 participants.

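### The primary time-by-group interaction is a change-score t-test whose power at 137 per group depends on an unstated correlation or scale; adjusting for baseline well-being would usually be more precise

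*Protocol article*

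**What the plan says.** Section 2.7 of the protocol article fixes the primary analysis. Repeated measures ANOVA "will be used to verify the interaction between time (pre- and post-intervention) and group (intervention and control groups") for subjective well-being. Before that, intervention and control participants are matched 1:1 on a logistic propensity score built from the baseline survey. Section 2.7 then adds: "In cases where the interaction is significant, a multiple comparison test will be performed using the Bonferroni method". It does not mention a regression of the outcome on baseline well-being.

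The sample size is in section 2.1. It starts from a review in which "positive psychology interventions showed an effect size of 0.34 for subjective well-being". For a t-test, "137 individuals were required in both the intervention and control groups" ("with a statistical power of 0.8 and a risk level of 0.05"). Attrition and response are then allowed for: "we estimated a dropout rate of approximately 20% over 2 years", and "the expected valid response rate at baseline and follow-up was approximately 80" percent. Finally, "The percentage of participants required in the intervention group was approximately 10% of the total participants". The resulting baseline survey size is 2675.

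The groups are not randomised. Section 2.1 assigns people by their own report, at follow-up, of having taken part in at least one activity. The primary outcome is a single 0 to 10 ladder item (section 2.3), collected at baseline with mean 7.2 and SD 1.9 (section 3).

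**The concern.** A t-test on change has a residual variance that depends on how strongly the baseline and 2-year scores correlate. The sample size calculation contains no such correlation. It also does not say which SD the effect size of 0.34 refers to. The article therefore does not show that the planned primary test has the stated 80% power.

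A second question is whether the interaction is the best use of data already collected. Baseline well-being can enter a regression as a covariate, which commonly gives a smaller standard error than the change score. It also corrects for baseline differences left after matching, if the groups are comparable given the baseline covariates.

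At stake are power, possible distortion from residual imbalance, and the reading of the follow-on comparisons in place of the interaction itself.

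**Working it through.** **Inputs.** From section 2.1: effect size d = 0.34, power 0.80, α = 0.05 (two-sidedness assumed; it reproduces the figure), 137 per group, dropout 20%, valid response 80% at each survey, intervention share 10%. From section 3: 2343 valid baseline responses. Not in the article: the pre-post correlation ρ, for which 0.3 to 0.7 is assumed.

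**1. The plan's own figures.** A two-sided two-sample t-test at d = 0.34 with 80% power needs 136.76, hence 137 per group (power 0.801). A one-sided test would need 107 by the normal approximation and does not match. For the survey size, 137 / (0.10 × 0.8 × 0.8 × 0.8) = 2675.8, which agrees with 2675. The arithmetic is sound.

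**2. Equivalence.** With two groups and two times, the interaction F equals the square of the t statistic on change. A numerical check on simulated data gave 0.9629 for both.

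**3. Power at 137 per group, if 0.34 is in SDs of the follow-up score.** Assume equal SDs at both times and balanced baselines.

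- Change score: variance 2(1 − ρ)σ², so the effective d is 0.34 / √(2(1 − ρ)).
- Baseline-adjusted: variance (1 − ρ²)σ², so the effective d is 0.34 / √(1 − ρ²).
- Variance ratio, adjusted to change: (1 − ρ²) / (2(1 − ρ)) = (1 + ρ)/2.

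| ρ (assumed) | d, change | Power, interaction | n per group for 80% | d, adjusted | Power, adjusted | n per group for 80% | Variance ratio |
|---|---|---|---|---|---|---|---|
| 0.3 | 0.287 | 0.66 | 192 | 0.356 | 0.84 | 125 | 0.65 |
| 0.4 | 0.310 | 0.73 | 164 | 0.371 | 0.86 | 116 | 0.70 |
| 0.5 | 0.340 | 0.80 | 137 | 0.393 | 0.90 | 103 | 0.75 |
| 0.6 | 0.380 | 0.88 | 110 | 0.425 | 0.94 | 88 | 0.80 |
| 0.7 | 0.439 | 0.95 | 83 | 0.476 | 0.975 | 71 | 0.85 |

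If 0.34 is instead in SDs of change, 137 per group is exactly right for the interaction at any ρ.

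**4. Effect of the achieved baseline return.** Applying the plan's own rates, 2343 × 0.10 × 0.8 × 0.8 ≈ 150 in the intervention group. At 150 per group the interaction has power 0.70 at ρ = 0.3, 0.76 at 0.4 and 0.835 at 0.5. The break-even ρ falls to about 0.45.

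**5. Limits of the precision ranking.** With a baseline imbalance of d₀ SDs and equal SDs, the variance ratio becomes (1 + ρ)/2 × [1 + n·d₀² / (2(2n − 2))]. At n = 137:

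- ρ = 0.5, d₀ = 0.1: ratio 0.752.
- ρ = 0.9, d₀ = 0.5: ratio 1.010.
- ρ = 0.7, d₀ = 1.0: ratio 1.064.

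With unequal SDs (s₀ at baseline, s₁ at follow-up) and balanced baselines, the change-score variance exceeds the adjusted one by (s₀ − ρs₁)². This is zero when the regression slope is 1. For example, s₀ = 1, s₁ = 1.25, ρ = 0.8 gives 0.5625 for both.

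**6. Residual imbalance.** Suppose there is no true effect and both groups regress to a common mean. The change-score contrast then has expectation −(1 − ρ)d₀. At ρ = 0.5 and d₀ = 0.1 this is −0.05 SD, and 0.05/0.34 ≈ 15% of the target effect. At d₀ = 0.5 a simulation gave −0.25 SD for the change score and about 0 for the adjusted estimate.

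**The case against.** Repeated measures ANOVA after matching is a valid prespecified test, and nothing here is an arithmetic error. Several objections stand in whole or part.

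- A reader might infer that 137 was computed for a different test. The article does not support that: it sized a t-test, and the interaction is a t-test. What is missing is the scale of 0.34 and the value of ρ.
- A reader might infer that the interaction is always less precise than baseline adjustment. It is not. The advantage vanishes at a regression slope of 1 and can reverse under large imbalance with high ρ. Those settings are mostly extreme after adequate matching.
- A power shortfall is not established. No ρ is given, a value below 0.5 is only plausible for a single item measured two years apart, and at ρ = 0.7 the interaction has 0.95 power.
- In a self-selected design, change-score and baseline-adjusted analyses can estimate different effects. The regression-to-the-mean figures assume a common mean, and other selection mechanisms can favour the change score.
- Section 2.7 does not say that baseline well-being is in the propensity model. If it is and matching works, residual imbalance and its bias are small.
- The Bonferroni comparisons follow only a significant interaction and are not described as within-group tests. The text therefore does not show an intention to claim an effect from pre-post change alone.

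**Conclusion.** The concern holds in a conditional form. The primary interaction is a change-score t-test. The 137 per group gives it at least 80% power if 0.34 is in SDs of change, or if it is in SDs of the score and ρ is at least 0.5; neither condition is stated. On the score scale, power runs from 0.66 to 0.95 over ρ from 0.3 to 0.7, against 0.84 to 0.975 with baseline adjustment. The adjusted variance is 15% to 35% lower over that range. These figures assume equal SDs and balanced baselines.

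Adjustment also corrects imbalance left after matching, under the assumption that the matching itself relies on: comparability given the baseline covariates.

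The Bonferroni step adds nothing to the test of effect, because the interaction has one degree of freedom and already is the between-group comparison of change. This is a matter of efficiency and clarity that should be addressed, not a demonstrated error in the sample size.

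**What to change.** - Include baseline well-being in the propensity model, and say so.
- Make the primary analysis a regression of 2-year well-being on group and baseline well-being, plus the matching covariates, in the matched sample. Report the adjusted difference with its 95% CI whether or not it is significant.
- Keep the time-by-group interaction as a sensitivity analysis, since the two can differ when groups are self-selected, and discuss any disagreement.
- State whether 0.34 is in SDs of the score or of change, and the pre-post correlation assumed.
- Do not use the post hoc Bonferroni comparisons as evidence of the intervention effect.

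The cost is wording in the analysis plan and a little more analysis work; baseline well-being is already collected. The downside is reliance on a linear relation between baseline and 2-year scores.

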## 3. Results

The self-administered questionnaires were distributed to 3742 eligible participants, from whom data were analyzed from 2503 participants (response rate: 66.9%). After excluding 160 questionnaires, including six from respondents living outside the designated areas, 62 questionnaires that were almost entirely blank, 72 that were missing essential identification labels (age or sex), and 20 from respondents who refused to participate in the survey, the analysis included data from 2343 individuals (1024 men and 1319 women; valid response rate: 62.6%).

Table 2 shows the baseline characteristics of the study population. The mean age was 74.4 (standard deviation, 5.4) years. The mean subjective well-being score was 7.2 (standard deviation, 1.9). Compared with women, men were significantly less likely to live alone; have less musculoskeletal pain; have lower subjective well-being, psychological health, activities of daily living, Dietary Variety Score, and Food Frequency Score; and have lower levels of social activities. Additionally, men were significantly more likely to be employed, socially isolated, and frail; have more current drinking and smoking habits; have higher health literacy and Motor Fitness Scale scores; and use the Internet more frequently.

Although physical function deteriorates with aging [54], subjective well-being can be maintained or promoted [22,55,56]. Higher levels of subjective well-being were observed in the participants in this study compared with those in the nationwide survey (the score was 6.2 in 2022) [57]. A previous study revealed that a higher density of older people in certain areas was associated with a higher level of subjective well-being [58]. Although the percentage of the population aged ≥65 years was lower in Chofu City than in Japan as a whole (21.6% vs. 28.9% as of 1 October 2021) [20,59], the participants had higher subjective well-being.

## 4. Discussion

To the best of our knowledge, the present study describes a unique intervention because it facilitates the formation of online and in-person communities; provides group-based online programs consisting of physical exercise, cognitive training, and nutrition lectures; establishes community hubs with psychological support from volunteers; and organizes multi-generational community events. These attempts to create connections for older adults may extend their healthy life expectancy, mediated by maintaining or promoting subjective well-being.

Previous reviews have indicated that ICT use can reduce loneliness and social isolation [60]; however, older individuals who use the Internet have a higher socioeconomic status than non-users [61]. In this baseline survey, the proportion of older adults using the Internet was lower than that in a national survey in Japan (60.1%) [62]. The promotion of Internet and ICT use through this intervention can allow community-dwelling older adults to obtain its benefits, leading to reduced social isolation.

This study has some limitations. First, the participation rate was not high compared to that in some cohort studies in the baseline survey [19,24,63]. Second, the low proportion of participants using the Internet, compared with a national survey in Japan, can potentially influence the results. Third, the study’s internal validity may have been affected by participants’ recall bias, as a self-administered questionnaire was used. Fourth, although the random selection of participants and the calculation of sample size for interventions would typically be performed, the present study was conducted as a quasi-experimental study. Finally, in this community-based intervention, there is a potential risk of contamination that could affect the accurate assessment of intervention effects, as both the intervention and control groups reside in the same area. Therefore, the fact that all participants belong to the same residential area may affect the results of the study.

The CDC movement was launched in 2022 to create connections to enhance subjective well-being among community-dwelling older adults. A multi-component intervention and the planned 2-year follow-up survey will be implemented. This study is expected to contribute to the development of a prototype strategy to promote the subjective well-being of older adults.

## 5. Conclusions

The community-based intervention trial (the Chofu-Digital-Choju movement) was launched in 2022 to improve the subjective well-being of community-dwelling older adults by fostering in-person and online connections. The insights of this study could contribute to the development of a prototype subjective well-being strategy for older adults.

## Figures and Tables

**Figure 1 healthcare-12-00322-f001:**
[figure not shown]
Geographical locations of the study areas (Chofu City, Tokyo, Japan).

**Figure 2 healthcare-12-00322-f002:**
[figure not shown]
Study flow diagram. * Participants will be categorized into either the intervention or control group based on their response in the follow-up survey regarding prior participation in any of the interventions. ** Propensity score matching with a ratio of 1:1 between the intervention and control groups will be applied using logistic regression based on the baseline survey.

**Table 1 healthcare-12-00322-t001:** Summary of the items surveyed at baseline, 2022.

**Primary outcome measures**
Subjective well-being
**Secondary outcome measures**
Psychosocial function
Social isolation
Neighborhood relationships
Social participation
Health literacy (CCHL)
Psychological health (WHO-5)
Depressive mood (GDS-5)
Physical activity and physical function
Exercise habits
Frailty status (CL15)
Activities of daily living (TMIG-IC)
Motor Fitness Scale
Dietary habits
Dietary Variety Score
Food Frequency Score
Eating alone
Use of ICT
Type of own ICT
Frequency of Internet usage
**Additional measures**
Age
Sex
Cohabiters
Years of residence in the neighborhood area
Financial status
Employment status
Chronic musculoskeletal pain (shoulder, low back, knee)
Body mass index (self-rated height and weight)
Drinking and smoking

CCHL: communicative and critical health literacy; WHO: World Health Organization; GDS-5: 5-item version of the Geriatric Depression Scale; CL15: Check-List 15; TMIG-IC: Tokyo Metropolitan Institute of Gerontology Index of Competence; ICT: information and communication technology.

**Table 2 healthcare-12-00322-t002:** Baseline characteristics of the participants.

Variables	All		Men		Women		*p*-Value
Number of residents aged 65–84 years old	3742		1681		2061		
Number of analyzed participants (eligible response rate; %)	2343	(62.6)	1024	(60.9)	1319	(64.0)	
Age, years, mean (SD)	74.4	(5.4)	74.2	(5.5)	74.5	(5.3)	0.094
65–74, *n* (%)	1232	(52.6)	564	(55.1)	668	(50.6)	
75–84, *n* (%)	1111	(47.4)	460	(44.9)	651	(49.4)	0.033
Living alone, *n* (%)	454	(19.5)	157	(15.4)	297	(22.7)	<0.001
Year of residence in the neighborhood, *n* (%)							
<29	718	(30.8)	337	(33.0)	381	(29.0)	
30–59	1407	(60.3)	561	(54.9)	846	(64.4)	
>59	209	(9.0)	123	(12.0)	86	(6.5)	<0.001
Financial status (self-rated), *n* (%)							
Low	76	(3.3)	42	(4.1)	34	(2.6)	
Middle-low	303	(13.0)	143	(14.1)	160	(12.2)	
Middle	888	(38.2)	361	(35.5)	527	(40.3)	
Middle-high	941	(40.5)	419	(41.2)	522	(39.9)	
High	118	(5.1)	52	(5.1)	66	(5.0)	0.055
Employment status, *n* (%)							
No	1537	(66.5)	581	(57.0)	956	(73.9)	
Yes	776	(33.5)	439	(43.0)	337	(26.1)	<0.001
Musculoskeletal pain (either shoulder, low back, or knee), *n* (%)							
No	792	(34.8)	391	(39.1)	401	(31.5)	
Yes	1482	(65.2)	610	(60.9)	872	(68.5)	<0.001
Body mass index, kg/m^2^, mean (SD)	22.7	(3.2)	23.3	(2.9)	22.2	(3.3)	<0.001
<18.5, *n* (%)	178	(7.8)	38	(3.8)	140	(10.9)	
18.5–24.9, *n* (%)	1632	(71.1)	719	(71.4)	913	(70.9)	
≥25, *n* (%)	485	(21.1)	250	(24.8)	235	(18.2)	<0.001
Alcohol drinking status, *n* (%)							
Never or former	1026	(44.0)	274	(26.8)	752	(57.4)	
Current	1307	(56.0)	749	(73.2)	558	(42.6)	<0.001
Smoking status, *n* (%)							
Never or former	2116	(90.8)	865	(84.7)	1251	(95.5)	
Current	215	(9.2)	156	(15.3)	59	(4.5)	<0.001
**Primary outcome measures**							
Subjective well-being, mean (SD)	7.2	(1.9)	6.9	(1.9)	7.4	(1.8)	<0.001
**Secondary outcome measures**							
Social relationships							
Social isolation, *n* (%)	1572	(68.6)	782	(78.1)	790	(61.2)	<0.001
Neighborhood relationships, *n* (%)							
Visiting each other	489	(21.8)	132	(13.3)	357	(28.4)	
Standing and chatting	921	(41.0)	344	(34.6)	577	(46.0)	
Exchanging of greetings	694	(30.9)	421	(42.4)	273	(21.8)	
None	144	(6.4)	96	(9.7)	48	(3.8)	<0.001
Social participation more than once a month, *n* (%)	1032	(44.6)	346	(34.1)	686	(52.9)	<0.001
Health literacy (CCHL), mean (SD)	3.6	(0.8)	3.6	(0.8)	3.5	(0.8)	0.028
Psychological health (WHO-5: 0–25), mean (SD)	15.0	(5.4)	14.6	(5.6)	15.3	(5.3)	0.004
Depressive mood (GDS-5 ≥2), *n* (%)	814	(36.0)	365	(36.8)	449	(35.5)	0.526
Physical activity and physical function							
Engaging in any exercise more than once a week, *n* (%)	1735	(76.8)	756	(76.1)	979	(77.4)	0.456
Engaging in walking 150 or more minutes per week, *n* (%)	1473	(65.0)	615	(62.1)	858	(67.2)	0.012
Going out more than once a day, *n* (%)	1504	(65.1)	672	(66.7)	832	(63.8)	0.136
Frailty (CL15 score ≥4), *n* (%)	497	(22.8)	252	(26.4)	245	(20.0)	<0.001
TMIG-IC (score: 0–13), mean (SD)	11.3	(1.8)	10.9	(2.1)	11.6	(1.6)	<0.001
Motor Fitness Scale, mean (SD)	10.5	(3.5)	10.9	(3.2)	10.1	(3.7)	<0.001
Dietary variety							
Dietary Variety Score (0–10), mean (SD)	3.4	(2.3)	2.8	(2.2)	3.9	(2.3)	<0.001
Food Frequency Score (0–30), mean (SD)	18.4	(5.2)	16.9	(5.1)	19.6	(4.9)	<0.001
Eat alone at least a whole day per week, *n* (%)	1041	(46.6)	442	(44.7)	599	(48.1)	0.112
Use of ICT							
Owing smartphone	1529	(66.2)	677	(67.0)	852	(65.6)	0.488
Using the Internet more than once a day, *n* (%)	1059	(46.7)	545	(54.6)	514	(40.5)	<0.001

CCHL: communicative and critical health literacy; WHO: World Health Organization; GDS-5: 5-item version of the Geriatric Depression Scale; CL15: Check-List 15; TMIG-IC: Tokyo Metropolitan Institute of Gerontology Index of Competence; ICT: information and communication technology; SD: standard deviation. Missing values were eliminated, and *p*-values were calculated using the chi-square test for categorical variables, and Welch’s *t*-test was employed to compare continuous variables between men and women.

## Data Availability

The data presented in this study are available on request from the corresponding author.
